## Abstract

**Background:**

The rate of caesarean sections around the world is rising each year, reaching epidemic proportions. Although many caesarean sections are performed for concerns about fetal welfare on the basis of abnormal cardiotocography, the majority of babies are shown to be well at birth, meaning that the operation, with its inherent short and long term risks, could have been avoided without compromising the baby’s health. Previously, fetal scalp blood sampling for pH estimation was performed in the context of an abnormal cardiotocograph, to improve the identification of babies in need of expedited delivery. This test has largely been replaced by lactate measurement, although its validity is yet to be established through a randomised controlled trial. This study aims to test the hypothesis that the performance of fetal scalp blood lactate measurement for women in labour with an abnormal cardiotocograph will reduce the rate of birth by caesarean section from 38 % to 25 % (a 35 % relative reduction).

**Methods/Design:**

Prospective unblinded randomised controlled trial conducted at a single tertiary perinatal centre. Women labouring with a singleton fetus in cephalic presentation at 37 or more weeks’ gestation with ruptured membranes and with an abnormal cardiotocograph will be eligible. Participants will be randomised to one of two groups: fetal monitoring by cardiotocography alone, or cardiotocography augmented by fetal scalp blood lactate analysis. Decisions regarding the timing and mode of delivery will be made by the treating team, in accordance with hospital protocols.

The primary study endpoint is caesarean section with secondary outcomes collected from maternal, fetal and neonatal clinical course and morbidities. A cost effectiveness analysis will also be performed. A sample size of 600 will provide 90 % power to detect the hypothesised difference in the proportion of women who give birth by caesarean section.

**Discussion:**

This world-first trial is adequately powered to determine the impact of fetal scalp blood lactate measurement on rates of caesarean section. Preventing unnecessary caesarean sections will reduce the health and financial burdens associated with this operation, both in the index and any future pregnancies.

**Trial registration:**

Australian New Zealand Clinical Trials Registry ACTRN12611000172909

## Background

There is currently an epidemic of caesarean sections performed in Australia and overseas [1]. Although many caesarean sections are performed for concerns about fetal welfare, the majority of babies are shown to be well at birth, meaning that the operation, with its inherent short- and long-term risks, could possibly have been avoided, without compromising the baby’s health. This project is a randomised trial of fetal scalp blood sampling for lactate measurement during labour, with a view to reducing the caesarean section rate for apparently non-reassuring fetal status. The trial proposal derives from the Cochrane systematic review of intrapartum fetal scalp blood sampling for lactate measurement [2], which highlighted the need for a randomised trial of its effectiveness.

It is imperative that a randomised controlled trial of lactate measurement be conducted so that potentially unnecessary caesarean sections can be avoided, that may otherwise harm, rather than help, mothers and their babies. As such, this will be a world-first trial.

### The burden of disease associated with caesarean sections

Despite the evidence that caesarean section rates above 15 % seem to do more harm than good [3], countries such as Australia, the United States of America and China report alarmingly high rates of 27-50 % [1, 4, 5]. The Australian caesarean section rate of 32 % translates to over 95,000 women having this surgery per year, with over 39,000 of these occurring following the onset of labour [4].

Risks that are increased with a caesarean birth include anaesthetic risks, maternal infection, venous thromboembolism, haemorrhage [6, 7] and intensive care unit admissions for babies with breathing difficulties [8]. Having had a caesarean section delivery increases risks in subsequent pregnancies of having further caesarean sections, stillbirth, rupture of the uterus, hysterectomy and increased bleeding due to the placenta implanting over the scar [9–11]. These concerns must be balanced against the need on occasions to urgently deliver a sick baby who would be compromised by remaining in the uterus.

A common indication for caesarean sections following the onset of labour is the identification of a non-reassuring fetal heart rate pattern. The chief investigator of this study has previously found that 38 % of Australian labouring women, where a non-reassuring fetal heart rate pattern had been identified, proceeded to delivery by caesarean section if no further testing of fetal well-being was performed (i.e. for pH or lactate). On the other hand, the caesarean section rate was 10 % when such testing was undertaken [12].

### Cardiotocography assessment of fetal well-being during labour

Cardiotocography (CTG), which detects and records the fetal heart rate by Doppler along with uterine contractions, was introduced into clinical practice in the 1960s with the aim of improving perinatal outcomes by improving intrapartum fetal welfare surveillance. A recent clinical audit revealed that 71 % of labouring women have continuous CTG in labour at the Royal Women’s Hospital, Melbourne. Fetal heart rate patterns can be classified in a number of ways. These include: (i) normal/reassuring; and (ii) when non-reassuring, a range of terms including non-reassuring, suspicious, atypical, abnormal, pathological or ominous. These classifications are based on the fetal heart rate, its variability and the presence of accelerations or decelerations, compared with the occurrence of uterine contractions. Several groups have published guidelines in an attempt to provide uniformity of interpretation [13–16]. Consistent with these guidelines and with the review team’s clinical practice, this protocol generally refers to “non-reassuring fetal status or abnormal /CTG/patterns”, rather than the term “fetal distress”, which is sometimes used inappropriately to refer to CTGs that do not meet normal/reassuring status [17]. Reassuring patterns require no specific action. Non-reassuring patterns are identified in approximately 15 % of those with CTG monitoring [18] and may prompt clinical actions ranging from simple manoeuvres, such as maternal position change, improved maternal hydration, through to expedited birth of the baby by caesarean section, forceps or vacuum. These actions aim to prevent or minimise hypoxia in the fetus.

### Compensation mechanisms for decreased oxygen supply: can the intrapartum CTG identify the baby’s response?

Non-reassuring CTG patterns may reflect adaptations made by the individual fetus to decreases in oxygen supply. Inadequate oxygen supply results in anaerobic metabolism of glucose, which leads to metabolic acidosis and the production of lactate. Low pH is a combined measure of both metabolic acidosis (including base deficit) and the more labile component, respiratory acidosis.

The differences in individual fetal responses to a decrease in oxygen (and therefore differences in fetal heart rate changes) mean that the positive predictive value of non-reassuring CTG for adverse outcome is low, although the negative predictive value of a reassuring pattern is high [18]. This means that a normal CTG almost always indicates reassuring fetal status, while a non-reassuring CTG on its own significantly overestimates the occurrence of babies that would have a poor perinatal outcome if birth were delayed. These features, combined with marked inter-observer variation in CTG interpretation by midwives and doctors, result in high caesarean section rates for non-reassuring fetal status in many hospitals [19, 20].

### Fetal scalp blood sampling

Collection of a small capillary blood sample from the fetal scalp (a fetal blood sample) for blood gas analysis has been used in clinical practice since the 1960s to assist in intrapartum fetal welfare evaluation [21]. Following identification of one abnormal or two non-reassuring features on the CTG, the National Institute for Health and Care Excellence in the United Kingdom recommends fetal blood sampling (FBS) for pH or lactate estimation, with a published action algorithm based on the result [14]. Following rupture of the amniotic membranes and at cervical dilatation greater than or equal to approximately 3 cm, an amnioscope is placed vaginally to allow adequate visualisation of the fetal head. A small sample of blood is then taken from the fetal scalp. This procedure may be uncomfortable and intrusive for the mother and is invasive to the baby. Rare complications include fetal scalp infection and haemorrhage [22, 23] and it is contra-indicated when the mother is known to have HIV or viral hepatitis, or where there is suspicion of a bleeding tendency in the fetus [23, 24].

Traditionally, such testing has required approximately 30 to 50 microlitres of blood, which is often difficult to obtain [25]. Even when the clinician is able to collect this quantity of blood, samples are frequently rejected by the testing equipment due to contamination with air or amniotic fluid. Some equipment can analyse for other components, such as lactate. Fetal lactate testing equipment requiring a much smaller blood volume (as little as 5 microlitres) is now available [26].

### Fetal blood sampling for pH estimation: what is the supporting evidence for use?

The Cochrane systematic review of intrapartum CTG for fetal welfare [27] reported that:In a meta-analysis of five RCTs enrolling 18,700 mother/baby pairs, the relative risk (RR) for caesarean section was 1.96 (95 % confidence intervals [CI] 1.23 to 3.09) for the continuous CTG group compared with intermittent auscultation of the fetal heart.Meta-analysis of six RCTs (*n* = 15,000) resulted in an RR of 1.5 (95 % CI 1.10 to 2.06) for caesarean section when fetal well-being was monitored by CTG and fetal scalp blood pH sampling, versus intermittent auscultation.Only one of the published RCTs compared outcomes following allocation to CTG + FBS (pH) or CTG alone: four of 229 women in the CTG + FBS group underwent caesarean section, compared with 41 of 230 in the CTG-only group, yielding a relative risk of 0.64 (95 % confidence intervals 0.40 to 1.00) [28]. There were no differences in any immediate infant outcomes (Apgar scores, cord blood gases, neonatal death, neonatal morbidity, nursery course).

These trials and the systematic review influenced obstetric opinion toward recommending FBS when a non-reassuring CTG is identified during labour, for example, the National Institute for Health and Care Excellence in the United Kingdom [14] clinical practice guidelines, which are closely aligned with Australian clinical practice. Not all countries follow this line of persuasion, however, with FBS for pH estimation being uncommon in the United States of America, for example [29].

The use of pH estimation in Australia has declined, largely replaced by the availability of hand-held bedside lactate testing units, which require much smaller blood samples than for pH.

### Fetal blood sampling for lactate measurement: an alternative to pH estimation

A fetal scalp blood sample for lactate measurement (FBSLM) taken within 60 min prior to birth correlates well with umbilical arterial and venous lactate, pH and base excess measured following birth [30]. Umbilical arterial (UA) lactate values correlate well with UA pH and base deficit values [30, 31].

Allen et al. [32] reported that fetal scalp lactate values greater than or equal to 4.2 mmol/L offered the best sensitivity and specificity for detecting clinically important outcomes. Kruger et al. [25] retrospectively examined the predictive values of 326 simultaneous fetal scalp blood estimations of lactate and pH for Apgar scores, umbilical arterial pH, umbilical arterial base deficit and neonatal encephalopathy. Cut-off values were the 75th centile for lactate (4.8 mmol/L) and the 25th centile for pH (7.20). The area under the receiver operating characteristic (ROC) curve was significantly greater for lactate than for pH in predicting neonatal encephalopathy and low Apgar score [25]. These findings and evidence from animal studies of the effects of lactate on brain tissue [33, 34] suggest that lactate estimation may be a better predictor of severe neonatal morbidity than pH.

### Lactate values that prompt clinical intervention

Because different lactate values can be simultaneously recorded from different lactate measurement systems [35–37], the cut-off lactate value selected to prompt clinical action must be considered specifically for the lactate meter in use [2, 37]. The available data support a lactate value greater than 4.8 mmol/L as a cut-off value for intervention when measured with the Lactate Pro (Arkray, Kyoto, Japan) [38], which is used at the RWH and included the RWH Clinical Practice Guidelines [39].

### Intrapartum lactate values

Observational studies suggest that fetal lactate concentrations are constant during the first stage of labour in the absence of hypoxia, and that intrapartum lactate measurements are better than estimations of pH for the prediction of severe neonatal morbidity [25, 33, 34, 40, 41]. Nordström [42] found that, on average, maternal lactate rose by 2 mmol/l per 30 min in the second stage of labour. Fetal lactate concentrations correlate positively with the duration of active pushing at a rate about half that of the maternal lactate (1 mmol/L per 30 min) [42]. The question of whether this lactate rise is driven by fetal hypoxia or derived from the mother was investigated by studying the arterio-venous lactate difference at birth. They found that the main contributor to the fetal lactate increase is the fetus itself, especially with prolonged second stage [42]. This is also supported by animal studies [43]. These findings suggest that fetal scalp lactate measurements remain an appropriate indicator of fetal hypoxia in second stage, particularly, for example, when the fetal head is relatively high in the mother’s pelvis and a dense epidural analgesia is in place that limits the mother’s ability to bear down and give birth to the baby in a short timeframe (i.e. minutes). The clinical appropriateness of performing a FBSLM in response to abnormal fetal heart rate monitoring in active/advanced second stage warrants consideration, where the option of assisting the birth with vacuum or forceps would be a reasonable option, achievable within minutes, rather than delaying this intervention to take a blood sample.

### Appraising the evidence for lactate measurement in labour: Systematic review

There is only one published systematic review of the clinical effectiveness and risks of fetal scalp lactate sampling used to assess fetal well-being in labour, in the presence of a non-reassuring CTG [2]. Only two randomised trials [38, 44] compared outcomes following fetal scalp blood sampling for pH or lactate measurement. Fetal scalp blood lactate estimation was more likely to be successfully undertaken than pH, with fewer scalp incisions and results available within 60 s. Larger blood volumes and longer test times were required for pH estimation. No randomised trials were identified that compared the use of CTG-only with CTG and lactate, although one ongoing trial has been identified (The SCALP trial [45]) during the process of updating the published Cochrane systematic review. This creates an untenable dilemma. Lactate measurement has essentially replaced pH estimation clinically, but there is no evidence from randomised trials and systematic reviews supporting its use. The value of using lactate measurements in labour without this evidence is uncertain, given the contribution that pH estimation has previously been shown to make for avoiding caesarean birth [46, 47].

### The need for a randomised trial of lactate for assessment of fetal well-being

It is proposed that undertaking this randomised trial is timely and mandatory because:Caesarean section following onset of labour is a major contributor to the alarmingly high overall caesarean section rate.Caesarean section increases maternal mortality and morbidity in the index and subsequent pregnancies.Caesarean section may increase fetal/neonatal morbidity in the index pregnancy.Fetal blood sampling following identification of a non-reassuring CTG was previously done for pH estimation and was considered the best option to reduce the risk of unnecessary caesarean sections in many clinical settings.Lactate measurement has replaced pH estimation as the test of choice by FBS in contemporary Australian clinical practice and also in many overseas centres.Although lactate measurement is possible and the technology readily available, it is not widely practiced in Australian and many overseas maternity centres – that is, a state of equipoise exists.There currently exists no RCT data establishing the benefits and risks of FBSLM in labour.There is therefore an urgent need for evidence about the benefits and risks of lactate measurement when a non-reassuring CTG has been identified in labour, to enable childbearing women and their clinicians to make an informed choice for mode and timing of birth.

## Methods/Design

### Aim

The primary aim of this randomised trial is to determine whether the addition of FBSLM during labours complicated by a non-reassuring fetal heart rate cardiotocography trace reduces the risk of birth by caesarean section, compared with monitoring by CTG alone.

### Hypothesis

When a woman in labour has a non-reassuring CTG, she has a 38 % chance of delivery by caesarean section [12]. We hypothesise that the addition of FSBLM will reduce this rate from 38 % to 25 %, which is a 35 % relative reduction.

### Study design

This randomised controlled trial conforms to Consort Statement standards [48] and is informed by the investigator team’s experience in the evaluation of technology for fetal welfare assessment [49–52]. The nature of the RCT necessitates non-blinding of clinicians and participants. The trial has been registered with the Australian and New Zealand Clinical Trials Register (registration number ACTRN12611000172909), and has been approved by the Human Research Ethics Committee of the Royal Women’s Hospital, Victoria, Australia – the single site in which the trial is to be conducted (Project 11/56).

### Inclusion criteria

Abnormal fetal heart rate trace in labour not improved with conservative measures (maternal position change, correction of maternal hypotension, decrease or cessation of oxytocin infusion) (Table 1)

**Table 1 Tab1:** Abnormal CTG trace eligible for further evaluation by fetal scalp blood sampling

Consistent with hospital, national and international guidelines [14, 16, 39] an abnormal CTG trace eligible for further evaluation by FBS is defined as:	
One or more of	● Baseline FHR <100 beats per minute (bpm) or >170 bpm
	● Variability absent or <3 bpm
	● Prolonged deceleration (>90s and <5 min)
	● Late decelerations
	● Complicated variable decelerations
Both of	● Baseline FHR between 100-109 or 161-170
	● Baseline FHR variability 3-5 bpm for > 40 minsAbility to give informed consent in EnglishSingleton pregnancyGestation ≥ 37 weeksCephalic presentationCervical dilatation ≥ 3 cmRuptured amniotic membranes

### Exclusion criteria

Planned caesarean sectionKnown viral infections where FBS is contraindicated (e.g. hepatitis, HIV)Situations requiring immediate delivery, e.g. significant intrapartum haemorrhage, cord prolapse, etc.Known significant fetal anomaly or bleeding disorder

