#### Opt-out consent

From August 2014, eligible women booked and receiving antenatal care at the Royal Women’s Hospital will be provided with written information about the trial at various gestations, including the fact that both using and not using lactate measurement are both common strategies at RWH and are accepted as appropriate by senior clinical staff. The women will be advised that, if they subsequently meet the inclusion criteria and none of the exclusion criteria during labour, they will be part of the trial unless they let the clinical or research staff know that they wish to opt-out. They can let the staff know in a number of ways: verbally, by telephone or email. This information is then recorded in the woman’s medical record and in a register, maintained by and accessible to the appropriate clinicians and researchers. Both opt-in and opt-out consenting processes will continue from August 2014.

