### Randomisation and group allocation

A researcher not otherwise involved with the trial will use computerised sequence generation with permuted block randomisation, stratified for parity (nulliparous, parous), to develop the randomisation sequence that will be applied through sequentially numbered, sealed, opaque envelopes. Those women whose CTGs meet the inclusion criteria will be randomised in a 1:1 ratio to the CTG-only group or the CTG + lactate group. Clinical care during labour and birth will continue with the woman’s obstetric and midwifery team. Neonatal care will be the provided by the neonatal team, according to national resuscitation guidelines.

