#### CTG + lactate group

Following identification of an eligible CTG (Table 1) and randomisation to the CTG + lactate arm, if a non-reassuring CTG persists despite measures for improving the CTG, the timing and options for delivery will incorporate a further evaluation of fetal well-being. Fetal blood sampling for lactate measurement will be undertaken, with resulting actions as per Table 2 (developed from the available evidence and aligned with the Clinical Practice Guideline of the RWH [39]).

**Table 2 Tab2:** Clinical management for lactate results in the CTG + lactate group

Lactate (mmol/L)	Action
<4.0 mmol/L	Repeat FBS in 1 hour if the FHR abnormality persists
4.0-4.8 mmol/L	Repeat FBS within 30 minutes or consider expediting the birth if rapid rise since last sample
>4.8 mmol/L	Urgent delivery indicated

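### Scalp sampling is contraindicated on suspicion of a fetal bleeding tendency, but the exclusion covers only a known disorder, so a suspected case can be randomised to sampling (minor safety point)

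*Protocol article*

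**What the plan says.** Three parts of the protocol article bear on this.

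- **The contraindication.** The Background section on fetal scalp blood sampling says the procedure should not be done "when the mother is known to have HIV or viral hepatitis, or where there is suspicion of a bleeding tendency in the fetus". The same section calls the procedure invasive to the baby and names haemorrhage among its rare complications.
- **The exclusion.** The last item under Exclusion criteria reads "Known significant fetal anomaly or bleeding disorder". A separate item excludes known viral infections for which sampling is contraindicated.
- **The route to sampling.** Under Opt-out consent, women are told that "if they subsequently meet the inclusion criteria and none of the exclusion criteria during labour, they will be part of the trial" unless they say they wish to opt out. Randomisation and group allocation then states: "Those women whose CTGs meet the inclusion criteria will be randomised in a 1:1 ratio". For the lactate arm, if the abnormal trace persists despite corrective measures, the section CTG + lactate group says "Fetal blood sampling for lactate measurement will be undertaken, with resulting actions as per Table 2".

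**The concern.** The Background sets two different thresholds in one sentence. For viral infection the mother must be known to be infected; for bleeding, suspicion about the fetus is enough. The exclusion list carries the first threshold over unchanged but raises the second from suspected to known. The rule that decides entry is then narrower than the contraindication it should implement.

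What is at stake is patient safety, on a small scale. A fetus with a suspected bleeding tendency is the one the contraindication is meant to protect. As written, the mother can be entered, under opt-out consent by default, and allocated to the arm defined by that procedure.

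**Working it through.** The article gives no figure to reproduce here; the check is a comparison of wording, followed by a simple allocation count.

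**1. Contraindication against exclusion**

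| Condition | Background, Fetal scalp blood sampling | Exclusion criteria | Match? |
|---|---|---|---|
| Viral infection | Known: "it is contra-indicated when the mother is known to have HIV or viral hepatitis" | Known infection, tied to sampling being contraindicated | Yes |
| Fetal bleeding | Suspected: "where there is suspicion of a bleeding tendency in the fetus" | Known: "Known significant fetal anomaly or bleeding disorder" | No, the exclusion is narrower |

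**2. Does another criterion close the gap?** No. The remaining exclusions are planned caesarean section, viral infection and situations needing immediate delivery. The inclusion criteria concern the trace, consent in English, singleton pregnancy, gestation, presentation, dilatation and membranes. The reference to sampling being contraindicated is attached only to viral infection, so it is not a general catch-all.

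**3. Does another reading of the exclusion close it?**

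- If *fetal* qualifies only the anomaly, *bleeding disorder* may include a maternal one. Suspicion about the fetus that rests on a known maternal disorder would then already be excluded, and the gap shrinks. Suspicion that does not rest on a known disorder remains uncovered.
- If *known* qualifies only the anomaly, which is the less natural reading, the text still requires a bleeding disorder. It does not say that suspicion is sufficient.

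**4. From entry to sampling.** A woman with a suspected case meets no written exclusion, so she is eligible. She is randomised 1:1. In the lactate arm, sampling follows if the abnormal trace persists, and the section describing that arm states no check for contraindications.

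**5. Size.** The probability of the CTG + lactate arm is 1/(1 + 1) = 0.50 per randomised woman. For k suspected cases among those randomised, the expected number allocated to sampling is k × 0.50. The value of k is an assumption, since the article gives no frequency.

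| Assumed k among 600 | Expected in sampling arm |
|---|---|
| 1 | 0.5 |
| 2 | 1 |
| 6 (1% of 600) | 3 |

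These are allocations. The number actually sampled would be lower wherever the trace recovers or a clinician withholds sampling.

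**The case against.** The strongest reply has four parts.

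- **The contraindication sits in the Background.** It is a general description drawn from cited sources, and the exclusion list is the only operative rule. This is true, but it does not reconcile the two. The article states when the procedure should not be done and then sets an entry rule that admits some of those cases.
- **Clinical safeguards exist.** Lactate-arm management is said to align with the hospital's practice guideline, and care stays with the woman's own team. Nothing obliges a clinician to sample against a contraindication. This stands as a reason to expect very little actual harm. However, the guideline is not shown, and the discretion that the article spells out concerns timing and mode of birth, not whether to sample in the lactate arm. The Compliance section audits sampling attempts and seeks to address barriers, so properly withheld sampling could be logged as non-compliance. Even where sampling is withheld, the woman has already been randomised to a strategy whose defining test she should not have. Intention-to-treat analysis deals with her data but not with her eligibility.
- **The article condenses a fuller protocol.** Detailed screening may well be described there. That would answer a complaint about something left out, but here both statements are present and they differ.
- **The size is assumed.** This also stands. The range of 1 to 6 women has no source in the article and only illustrates scale. The case rests on the wording.

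**Conclusion.** The concern holds as a minor safety point. The exclusion is narrower than the article's own contraindication, and no other criterion or reasonable reading removes the difference entirely. The women affected are those with a suspected fetal bleeding tendency that does not rest on a known disorder; if only a fetal disorder counts under the exclusion, suspicion arising from a known maternal disorder is uncovered too. They are probably very few. On an assumed 1 to 6 among 600, 0.5 to 3 would be expected in the sampling arm, and fewer would be sampled.

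The conclusion rests on reading the exclusion list as the rule that decides entry, which is how the opt-out section uses it. Confidence is moderate, because the full protocol and the hospital guideline are not available and may prevent sampling in practice. They would not correct the stated criterion. No consequence for power, the primary estimate or the analysis is claimed.

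**What to change.** Reword the last exclusion, and apply it before randomisation, as:

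> Known significant fetal anomaly; known bleeding disorder; or suspected fetal bleeding tendency (including because of a maternal or family bleeding disorder).

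This brings the entry rule into line with the contraindication. It leaves *bleeding disorder* unrestricted, so nobody already excluded, through a maternal disorder for example, becomes eligible by accident. It also settles which words qualify which, which helps staff who apply the list during labour.

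The cost is a short edit to one criterion and a negligible loss of eligible women, made up by continuing recruitment to 600. The sample size and analysis need no change.
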